#### **4. LIST OF ABBREVIATIONS AND DEFINITIONS**

|              |                                               |
|--------------|-----------------------------------------------|
| CASI  | Computer Assisted Structured Interview        |
| ADCC  | Antibody Dependent Cell-Mediated Cytotoxicity |
| AE    | Adverse Event                                 |
| AIDS  | Acquired Immunodeficiency Syndrome            |
| ALT   | Alanine Transaminase                          |
| API   | Active Pharmaceutical Ingredient              |
| AST   | Aspartate Aminotransferase                    |
| BUN   | Blood Urea Nitrogen                           |
| BV    | Bacterial Vaginosis                           |
| CBC   | Complete Blood Count                          |
| CBR   | CBR International Corporation, Boulder CO     |
| CDC   | Complement Dependent Cytotoxicity             |
| CRF   | Case Report Form                              |
| CT    | Chlamydia trachomatis                         |
| CVF   | Cervicovaginal Fluid                          |
| CVL   | Cervicovaginal Lavage                         |
| DAERS | DAIDS Adverse Experience Reporting System     |
| DAIDS | Division of AIDS                              |
| EAE   | Expedited Adverse Event                       |
| EC50  | 50% Effective Concentration                   |
| FDA   | (United States) Food and Drug Administration  |
| GC    | Neisseria gonorrhoeae                         |
| GCP   | Good Clinical Practice                        |
| HCG   | Human Chorionic Gonadotropin                  |
| HEC   | Hydroxyethylcellulose                         |
| HIV-1 | Human Immunodeficiency Virus, Type 1          |

|                     |                                                          |
|---------------------|----------------------------------------------------------|
| HSV-1, HSV-2 | Herpes Simplex Virus Type 1, Type 2                      |
| IND          | Investigational New Drug application                     |
| IRB          | Institutional Review Board                               |
| ITT          | Intent-To-Treat                                          |
| IUD          | Intrauterine Device                                      |
| MAb          | Monoclonal Antibody                                      |
| MEMS         | Medication Event Monitoring System                       |
| N-9          | Nonoxynol-9                                              |
| NAAT         | Nucleic Acid Amplification Test                          |
| NIAID        | National Institute of Allergy and Infectious Diseases    |
| NIH          | National Institutes of Health                            |
| OHRP         | Office of Human Research Protections                     |
| PCR          | Polymerase Chain Reaction                                |
| PI           | Principal Investigator                                   |
| PP           | Per Protocol                                             |
| PSRT         | Protocol Safety Review Team                              |
| PVA          | Polyvinyl Alcohol                                        |
| RSC          | Regulatory Support Center                                |
| RT           | Reverse Transcriptase                                    |
| SHIV         | Engineered Hybrid Virus with HIV-1 Envelope and SIV Core |
| SLPI         | Secretory Leukocyte Protease Inhibitor                   |
| SOP          | Standard Operating Procedure(s)                          |
| STI          | Sexually Transmitted Infection                           |
| WB           | Western Blot                                             |
| VCF          | Vaginal Contraceptive Film                               |

## 5. PROTOCOL SUMMARY

### Protocol Summary

|                                           |                                                                                                                                                                                                                                                                                                                                                                                                                                                                                                                                                                                                                                                                                                                                                                                                                                                                                                                                                                                                                                                                                                                                                                                                                                                                                            |
|-------------------------------------------|--------------------------------------------------------------------------------------------------------------------------------------------------------------------------------------------------------------------------------------------------------------------------------------------------------------------------------------------------------------------------------------------------------------------------------------------------------------------------------------------------------------------------------------------------------------------------------------------------------------------------------------------------------------------------------------------------------------------------------------------------------------------------------------------------------------------------------------------------------------------------------------------------------------------------------------------------------------------------------------------------------------------------------------------------------------------------------------------------------------------------------------------------------------------------------------------------------------------------------------------------------------------------------------------|
| Protocol Title:                    | An early Phase 1, Single Center Study to Assess the Safety of MB66, a Combined Anti-HIV (VRC01-N) and Anti-HSV (HSV8-N) Monoclonal Antibody Film for Vaginal Application as Microbicide (MB66-01)                                                                                                                                                                                                                                                                                                                                                                                                                                                                                                                                                                                                                                                                                                                                                                                                                                                                                                                                                                                                                                                                                          |
| Short Title                        | Safety of MB66 Vaginal Film                                                                                                                                                                                                                                                                                                                                                                                                                                                                                                                                                                                                                                                                                                                                                                                                                                                                                                                                                                                                                                                                                                                                                                                                                                                                |
| Sample Size                        | 38 evaluable participants                                                                                                                                                                                                                                                                                                                                                                                                                                                                                                                                                                                                                                                                                                                                                                                                                                                                                                                                                                                                                                                                                                                                                                                                                                                                  |
| Population                         | Healthy, HIV-uninfected women, 18 – 45 years of age, at low risk of HIV/STI acquisition, who have normal menstrual cycles                                                                                                                                                                                                                                                                                                                                                                                                                                                                                                                                                                                                                                                                                                                                                                                                                                                                                                                                                                                                                                                                                                                                                                  |
| Participating Site                 | Miriam Hospital, Providence, RI                                                                                                                                                                                                                                                                                                                                                                                                                                                                                                                                                                                                                                                                                                                                                                                                                                                                                                                                                                                                                                                                                                                                                                                                                                                            |
| Study Design                       | 
This is a Pre-Phase 1, single center study with two sequential Segments:
 
Segment A: Single arm, single dose, study with 8 evaluable women and a pause for safety assessment upon completion and before initiation of Segment B.
 
Segment B: Two arm, repeated dose, randomized, single blind, placebo-controlled trial with 15 evaluable women per arm
 
The study will enroll approximately 43 women to reach a total of 38 evaluable women by the end of the study. Evaluable Segment A participants will be defined as those who complete the Screening and Enrollment Visits and return for the Day 1 visit. Evaluable Segment B participants will be defined as those who complete the Screening and Enrollment Visits and return for Visit 4 and are found by MEMS recordings to have used study product for at least 5 of the previous 7 days including the day before presentation. Non-evaluable participants will be replaced.
 
Accrual of 38 evaluable participants (8 in Segment A, 30 in Segment B) is expected to take 12 months. The expected duration of study participation for each participant will be approximately 5 to 9 weeks, including the screening period. After enrollment, the study duration will be 1-3 weeks.
 |
| Schedule of Procedures/Evaluations | A Day 0 dose will be placed in the study clinic in both Segments, and six additional doses will be inserted at home on Days 1-6 in Segment B. PK and safety evaluations will be done on Day 0, Day 1, and Day 7 in both Segments, and additionally on Day 14 for Segment B.                                                                                                                                                                                                                                                                                                                                                                                                                                                                                                                                                                                                                                                                                                                                                                                                                                                                                                                                                                                                                |

|                                   |                                                                                                                                                                                                                                                                                                                                                                                                                                                                                                                                                                |
|-----------------------------------|----------------------------------------------------------------------------------------------------------------------------------------------------------------------------------------------------------------------------------------------------------------------------------------------------------------------------------------------------------------------------------------------------------------------------------------------------------------------------------------------------------------------------------------------------------------|
| Study Duration             | Estimated total study duration 12 months, individual participation 5-9 weeks                                                                                                                                                                                                                                                                                                                                                                                                                                                                                   |
| Study Regimen/Intervention | 
MB66 film: Active film contains 10 mg of VRC01-N and 10 mg of HSV8-N monoclonal antibodies (MAbs). In Segment A the single exposure dose will be 1 film (10 mg of each antibody). In Segment B seven daily doses of one film (10 mg of each antibody) will be given to active film recipients, and supplied in MEMS capped (adherence monitoring) vials.
 
Placebo film: A vehicle control film with same excipients as the active film will be given to the placebo group in Segment B (one film daily for seven consecutive days).
 |
| Primary Objective          | To evaluate the safety of the MB66 film                                                                                                                                                                                                                                                                                                                                                                                                                                                                                                                        |
| Secondary Objectives       | 
To measure pharmacokinetic parameters including:
 
 
The rate of MB66 film dissolution
 
The vaginal concentrations of the MB66 antibodies
 
The degree of systemic absorption of the MB66 antibodies
 
                                                                                                                                                                                                                                                                                       |
| Exploratory Objectives     | 
To assess the antiviral effect of the MB66 antibodies ex vivo in cervicovaginal lavage fluid from participants after dosing with MB66 film
 
To compare the effects of MB66 and placebo films on the cervicovaginal microbial environment using pH, Nugent score, and bacterial ribosomal DNA PCR
 
To compare the effect of MB66 and placebo films on cervicovaginal immune mediators by Luminex and ELISA assays
 
To assess the acceptability of the MB66 vaginal film after 7 days of use
                                     |
| Primary Endpoint           | Incidence of Grade 2 or higher Adverse Events deemed related to study product                                                                                                                                                                                                                                                                                                                                                                                                                                                                                  |
| Secondary Endpoints        | 
Naked eye visual assessment during speculum exam of the degree of film dissolution at 1, 4, and 24 hours after dosing
 
Concentrations of MB66 antibodies in vaginal fluid sampled with Tear Flo (filter paper) wicks, and measured by ELISA
 
Concentrations of MB66 antibodies in serum by ELISA
                                                                                                                                                                                                                                            |

|                              |                                                                                                                                                                                                                                                                                                                                                                                                                         |
|------------------------------|-------------------------------------------------------------------------------------------------------------------------------------------------------------------------------------------------------------------------------------------------------------------------------------------------------------------------------------------------------------------------------------------------------------------------|
| Exploratory Endpoints | Assays of the ex vivo viral neutralization of HIV-1 and HSV-2 in cervicovaginal lavage fluid after MB66 dosing
Vaginal pH
Nugent score on Gram stained vaginal smears
Vaginal microbiome assessment by polymerase chain reaction (PCR) for bacterial ribosomal DNA (samples stored for later analysis)
Levels of immune mediators in cervicovaginal lavage fluid measured by Luminex and ELISA immunoassays |
|------------------------------|-------------------------------------------------------------------------------------------------------------------------------------------------------------------------------------------------------------------------------------------------------------------------------------------------------------------------------------------------------------------------------------------------------------------------|

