**Preclinical safety and vaginal pharmacokinetic studies**

Tissue cross reactivity: LeafBio has carried out tissue cross reactivity studies against a panel of human tissues with VRC01-N and HSV8-N. The panel included the following tissues: adrenal gland, heart, salivary gland, kidney, skin, blood cells, liver, spinal cord, blood vessels, lung, spleen, bone marrow, lymph node, striated muscle, brain (cerebellum, cerebral cortex), pancreas, thymus, breast, parathyroid, thyroid, colon, peripheral nerve, tonsil, eye, pituitary, bladder, ureter, ovary, fallopian tube, placenta, uterus (cervix, endometrium), testis, and prostate. Although no cross reactivity was observed with HSV8-N, positive staining in several tissues was observed with VRC01-N. The majority of this staining was cytoplasmic, however extracellular staining was observed in renal tissue from two of three sources. In the extracellular proteinaceous material in kidney, rare to occasional staining was observed at the 20 µg/mL concentration of VRC01-N, and rare staining was observed at the 2 µg/mL concentration of VRC01-N, (Table 1).

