**Table 13: Segment B, Visit 4 Procedures (Follow-up at Day 7)**

| Component                | Procedure/Analysis                                                                                                                                                                                                                                            |
|---------------------------------|----------------------------------------------------------------------------------------------------------------------------------------------------------------------------------------------------------------------------------------------------------------------|
| Administrative/Interview | Visit 4 Interview
Adverse event collection
Update concomitant medication log
Receive returned unused films
HIV pre- and post-test counseling
Acceptability interview (CASI)
Abstinence counseling
Schedule Visit 5 appointment
Reimbursement |
| Urine                    | Dipstick Urinalysis
Pregnancy test (HCG)
NAAT for chlamydia, gonorrhea, and trichomonas Δ                                                                                                                                                           |

| Component                            | Procedure/Analysis                                                                                                                                                                                                                                                                                                                                                |
|--------------------------------------|-------------------------------------------------------------------------------------------------------------------------------------------------------------------------------------------------------------------------------------------------------------------------------------------------------------------------------------------------------------------|
| Blood                         | Serum for study product MAb levels
Complete blood count Δ
AST, ALT, Creatinine Δ
Syphilis screen (RPR) Δ
Confirmatory HIV testing Δ                                                                                                                                                                       |

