| Physical Exam                 | Focused physical exam
Vital signs (temperature, blood pressure, heart rate)                                                                                                                                                                                                                                                                                    |
| Pelvic                        | Gynecologic exam including visual inspection of external genitalia and speculum exam
Vaginal swab for pH
Vaginal swab for Gram stain
Vaginal swab for microbiome PCR
CVF via Tear Flo MAb levels (cervical os, ectocervix, mid vagina, distal vagina), and visual assessment of degree of film dissolution
Vaginal swabs for wet prep † |
| CVL                           | Anti-viral activity, MAb levels, and immune mediators                                                                                                                                                                                                                                                                                                             |
| Δ If clinically indicated |                                                                                                                                                                                                                                                                                                                                                                   |

#### 11.1.2.7 Segment B, Visit 5: Exit Visit, Day 14

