The final scheduled visit will be targeted for Day 14, one week after completing seven daily doses of film. The window period for Visit 5 will extend from Day 12 to Day 16 inclusive. During the visit participants will be interviewed for AEs, evaluated for safety endpoints by pelvic exam and safety blood tests. Pharmacokinetic sampling of blood and vaginal Tear Flo samples and CVL will be obtained to assess MAb levels and distribution. CVL will also be assayed for antiviral activity, MAb levels, and immune mediators. Vaginal swabs will be used to assess vaginal pH, Nugent score, and microbiome by PCR. All vaginal sampling (swabs, Tear Flo strips, CVL) will be done via speculum. Participants will be reminded they are required to use condoms during all vaginal intercourse until Study Day 28 (three weeks after their last film administration). In the event of an unresolved AE requiring follow-up, an additional ad hoc visit (Section 11.2.4) will be scheduled. Visit 5 procedures are detailed in Table 14.

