## 14.4 STUDY ENDPOINTS

### 14.4.1 Primary Endpoint: Grade 2 Adverse events

The primary safety endpoint is the clinical or laboratory evidence of a Grade 2 or higher Adverse Event that is judged to be related to study product. Adverse events will be graded according to the following reference: *Division of AIDS (DAIDS) Table for Grading the Severity of Adult and Pediatric Adverse Events, Version 2.0, Nov 2014*, and the Female Genital Grading Table for Use in Microbicide Studies (Addendum 1 to the DAIDS Table for Grading Adult and Pediatric Adverse Events, Version 1.0, November 2007 [Clarification dated August 2009]).

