## **14.5 BLINDING**

Segment A will be open label since all participants will receive active film. Segment B participants will be blinded to assignment of active drug versus placebo. Because the active and placebo films are not identical in appearance, study staff cannot reliably be blinded to assignment, and hence we characterize Segment B as “single blind”. However, we will attempt to maintain blinding to assignment during laboratory testing, and among data recording and data analysis teams.

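### In Segment B the blood tests that feed the primary safety endpoint are optional at the end of dosing, and the first panel fixed for every woman comes about 5 to 10 days after the last film

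*Protocol*

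**What the plan says.** - **Endpoint.** Section 14.4.1 defines the primary endpoint as "clinical or laboratory evidence of a Grade 2 or higher Adverse Event that is judged to be related to study product". Laboratory findings therefore count.
- **Segment B, Visit 4 (Day 7, window to Day 8).** Section 11.1.2.6 times this visit at about 24 hours after the last film. The blood row of Table 13 reads "Complete blood count Δ AST, ALT, Creatinine Δ", and the footnote to the mark is "Δ If clinically indicated". Table 20 agrees, and Table 12 treats the Day 1 bloods in the same way. Serum for antibody levels is drawn from every woman at Visit 4.
- **Segment B, Visit 5.** The same tests are unconditional (Tables 14 and 20). Section 11.1.2.7 states: "The window period for Visit 5 will extend from Day 12 to Day 16 inclusive".
- **Segment A.** The panel is unconditional at the exit visit, Day 6 to 10 (Table 9 and Section 11.1.1.6).
- **Blinding.** Section 14.5 says that "study staff cannot reliably be blinded to assignment". Section 10.3 gives the reason: the two films differ in translucency.
- **Evaluability.** Section 14.2 requires a Segment B woman to return for Visit 4 with adequate film use. It does not require Visit 5. Section 14.7.5 uses the evaluable women for the primary analysis.
- **Summary.** Section 5 states: "PK and safety evaluations will be done on Day 0, Day 1, and Day 7 in both Segments". It adds Day 14 for Segment B.

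**The concern.** Segment B is the only part of the trial with repeated dosing, and its primary analysis asks whether a 30% rate of related Grade 2 or higher events (AE2) can be ruled out in each arm. The laboratory part of that endpoint is captured unevenly, in three ways.

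1. **Timing.** At the visit closest to the end of dosing, blood count, liver enzymes and creatinine depend on a clinical prompt. A change that causes no symptoms and resolves before Visit 5 leaves no record. Creatinine is among these tests, and Section 6.1.3 reports for VRC01-N that "extracellular staining was observed in renal tissue from two of three sources".
2. **Discretion.** The staff who decide whether a test is indicated may know the arm, so laboratory events could be looked for more often in one arm than in the other.
3. **Evaluability.** A woman who attends Visit 4 and misses Visit 5 can be counted among the 15 as free of laboratory events although no scheduled post-dose panel was taken.

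Missed events lower the observed rate and so make it easier to conclude that the film is safe. The enrolment pause rule in Section 13.8, which reacts to a related Grade 3 or higher event, also works only on events that are detected.

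**Working it through.** **Step 1. Time from last film to the first fixed panel.** Inputs: Table 4 and Sections 10.3, 11.1.1.6 and 11.1.2.7.

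| Segment | Last film | Fixed panel | Days after last film |
|---|---|---|---|
| A | Day 0 | Day 6 to 10 | 6 to 10 |
| B, Visit 4 on Day 7 | Day 6 | Day 12 to 16 | 6 to 10 |
| B, Visit 4 on Day 8 | Day 7 | Day 12 to 16 | 5 to 9 |

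Across Segment B the gap is 5 to 10 days (12 − 7 = 5; 16 − 6 = 10). Counted from the last film, Segment A is no earlier. Neither Segment fixes a panel within five days of a film.

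**Step 2. Reproduce the plan's rule.** The one-sided 95% Clopper-Pearson upper limit for x events in n is the 0.95 quantile of Beta(x + 1, n − x).

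- 0 of 15: 18.1%
- 1 of 15: 27.9% (Section 14.2 states 27.9%)
- 2 of 15: 36.3%

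So 30% is ruled out with 0 or 1 events in 15, as Section 14.7.2 says. The stated figures are correct. What matters here is how many events reach the count.

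**Step 3. Sensitivity of the rule to missed events.** Let the true AE2 rate be 30%, and let m be the share of all AE2s that is never detected. The documents give no value for m, so it is an assumption. The detected rate is p = 0.30 × (1 − m), and

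P(0 or 1 of 15) = (1 − p)^15 + 15 p (1 − p)^14.

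| m | p | P(30% wrongly ruled out) |
|---|---|---|
| 0 | 0.300 | 3.5% |
| 7% | 0.279 | 5.0% |
| 10% | 0.270 | 5.8% |
| 25% | 0.225 | 11.7% |
| 50% | 0.150 | 31.9% |

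**Step 4. What would produce such values of m.** Write m = L × (1 − s). L is the share of AE2s that are symptom-free laboratory changes present at the end of dosing. The share s of these is still present at Visit 5. Take s = one third, again an assumption, and suppose that no Day 7 test is prompted.

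- L = one tenth: m = 0.1 × 2/3 = 6.7%, p = 0.280, chance 5.0%.
- L = one third: m = 1/3 × 2/3 = 22.2%, p = 0.233, chance 10.3%.
- L = 1: m = 66.7%, p = 0.100, chance 54.9%.

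The last line requires every primary-endpoint event to be a silent blood abnormality. It is a limit, not a planning case.

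**Step 5. Unequal detection between arms.** Take equal true rates of 30%, full detection in the active arm, 15 women per arm and Fisher's exact test at two-sided 0.05. Full enumeration gives a rejection rate of 1.7% with full detection in the placebo arm, 2.9% with 75% and 7.8% with 50%. These detection shares are also assumptions.

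**The case against.** **The summary sentence.** A reader might infer that the Protocol Summary promises Day 7 bloods and that Table 13 breaks the promise. The documents do not support this. The sentence speaks of safety evaluations and names no blood test. It also covers Day 0 and Day 1, when neither Segment has a fixed panel. At Day 7 every Segment B woman does have safety evaluations.

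**The comparison with Segment A.** A reader might infer that Segment A is better monitored because its panel is fixed around Day 7. Step 1 shows that its panel falls equally late after the film. Both Segments share the same concept, one exit panel about a week after last exposure.

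**The renal staining.** Section 6.1.3 also gives the sponsor's own assessment that this is not a concern for a topical product with low systemic uptake, and serum was below the assay limit in the rabbit and rat studies. Large numbers of silent laboratory events are therefore not expected. This argues for a small m. It does not explain why the end-of-dosing panel is left to discretion.

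**Bias between arms.** Section 14.7.2 calls the Fisher comparison exploratory, and the 30% rule is applied within each arm. Extra testing of active-arm women would also work against a favourable conclusion. Unequal detection is a possibility that the design allows; the documents do not show that it occurs.

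**Visit 5.** A change that persists is caught by the fixed panel in both arms, provided that the woman attends. Only changes that have resolved, or women who do not attend, escape.

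All of this stands. It limits the size of the point. It does not remove the gap between an endpoint that counts laboratory events and an end-of-dosing visit that may not measure them.

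**Conclusion.** The concern holds as a weakness in how the primary endpoint is ascertained in Segment B. It is not an internal contradiction. Between the first film and Day 12, no blood count, AST, ALT or creatinine is fixed for Segment B women. The discretionary tests in that interval are ordered by staff who may know the arm. Evaluability does not secure the one fixed post-dose panel.

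The size cannot be settled from the document, which gives neither the laboratory share of AE2s nor how long such events last. With 7 to 25% of all AE2s missed, the chance of wrongly ruling out a true 30% rate is about 5 to 12%, against 3.5% with full detection. It reaches 32% only if half are missed. Figures near 55% require all AE2s to be silent laboratory changes with two thirds of them gone by Visit 5, and nothing in the protocol supports that. Failure to detect events pushes the within-arm result towards safe. The direction of any effect on the comparison of arms is open.

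**What to change.** 1. In Tables 13 and 20, make blood count, AST, ALT and creatinine at Segment B Visit 4 a fixed test for all women, taken from the existing venepuncture for serum antibody levels. Every evaluable woman attends Visit 4, so this also closes the gap left by the evaluability definition.
2. State that every related Grade 2 or higher laboratory result counts in the primary endpoint, including results from panels done because they were indicated. Excluding those would conflict with Section 14.4.1 and would lower the event count.
3. Report the number of discretionary panels by arm, and add a sensitivity analysis that uses laboratory events from the scheduled panels only.

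The cost is about 30 routine panels (15 women in each of two arms) and a slightly larger blood volume, so the total in Section 11.5.5 should be checked. No extra visit or needle-stick is needed. The observed AE2 rate may come out less favourable, because more events can be seen.
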